#### **9.5 Reporting of Serious Adverse Events/Serious Adverse Drug Reactions**

**Serious adverse events, which include SUSARs, are to be reported to the sponsor for the entire study period. SUSARs are reported even after the trial is over, if the sponsor, local medical monitor or principal investigator becomes aware of them.** The site will be provided with specific reporting procedures including the Adverse Event CRF and any supplemental reporting forms to be used. Serious adverse events will be reported on the Adverse Event CRF using a recognized medical term or diagnosis that accurately reflects the event.

Serious adverse events will be assessed by the investigator as described in Section 9.1.1 for severity, causal relationship to the study vaccine, and expectedness. The onset and resolution dates of the event and the action taken in response to the event will be documented. If the event has not resolved by the final study visit, it will be documented as “ongoing” on the CRF, however, follow-up of the SAE must continue until resolved. Information recorded on the CRF must be substantiated in the source documents.

The AE CRF containing a serious adverse event and the SAE Report completed for that event must be **faxed** by the principal investigator or his/her designee **within 24 hours** (one calendar day) of the investigative site becoming aware of the event to the local medical monitor and to Triclinium. The AE CRF should be completed with all information known at the time and a hard copy printed for faxing; the SAE Report (paper form) should be completed and both forms faxed (even if all information concerning the event is not yet known) within the first 24 hours of awareness of the event.

All serious adverse events that the investigator suspects are related to the study vaccine (SUSARs) should be **telephoned to the local medical monitor and to Triclinium immediately upon the investigator’s awareness of the event**. Since the principal investigator will be blinded for this study, in the event of an emergency where knowledge of the treatment allocation is required for proper clinical management of the subject, the PI may require the un-blinding of the treatment assignment (active treatment or placebo). If possible, sponsor approval should be sought prior to any emergency un-blinding procedure.

Contact information for all safety personnel are contained in the Team Contact List which will be stored on site in the investigator Site File and maintained by Triclinium.

Investigators **must not wait** to collect additional information to fully document the event before notifying the local medical monitor and Triclinium of a serious adverse event. The initial notification should include the following (at minimum):

- Protocol number and name and contact number of the investigator
- Subject study number (and initials and date of birth, if available)
- Date/s subject received study vaccine
- Serious adverse event(s) and date of event onset
- Current status of subject

ISS has authorized Triclinium to execute its responsibilities for safety report submission to the appropriate regulatory authorities within specific time periods of being notified of the event; the investigative site is responsible for notification of all SAE reports to the relevant Ethics Committee within the appropriate reporting time periods. Triclinium will notify the DSMB of all SAEs within three working days of becoming aware of an event and will provide all follow-up information in a timely manner.

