#### **9.1.2 Study Sponsor**

The Sponsor has an institutional responsibility to ensure subject safety. This responsibility is vested in a Data Safety Monitoring Board.

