##### **9.1.2.1 Local Medical Monitor (LMM)**

The LMM is the sponsor's representative and is a registered medical practitioner in his/her country of residence with experience in HIV/AIDS related research and HAART treatment. The LMM will regularly review all safety data while being cognizant of the known adverse reactions caused by drugs used in antiretroviral combination therapy. The LMM may assist the Principal Investigator in the assessment of severity and causality for adverse events, and help the PI in exploring the possibility of any "antiretroviral drug exchange" that may have been practiced by the subject. In addition to the ongoing review of adverse events, the LMM, by virtue of his/her location will be immediately available to discuss the significance and possible impact of a SUSAR/SAE with the principal investigator. The LMM, like the principal investigator, will be blinded.

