##### **9.1.2.1.1 Study Vaccine Pausing Rules for the Local Medical Monitor**

In the event of a safety concern the Local Medical Monitor in collaboration with the Principal Investigator will request that the Sponsor convene an ad hoc review of the relevant safety data

by the DSMB. Based on this review, the DSMB may choose to pause further vaccine administration in the study (See Section 10.)

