## **10 STUDY PAUSE/STOPPING RULES**

### **10.1 General rules for a study pause**

The Sponsor will appoint an independent DSMB to monitor the safety of the subjects enrolled in the study. The DSMB will review all serious adverse events reports in real-time and will receive periodic reports of all non-serious adverse events; the DSMB may un-blind any amount of safety information needed to conduct their assessments. The DSMB will determine whether the study should be continued, modified or stopped for safety concerns. Guidelines for making such a decision will be developed by the Sponsor in consultation with the DSMB.

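### Protocol 10.1 promises real-time DSMB review of every SAE report, but 9.5 allows three working days to notify the DSMB, with no shorter limit for related, fatal or life-threatening events

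*Protocol*

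**What the plan says.** Protocol 9.1.2 states the sponsor's duty to protect subjects and adds: "This responsibility is vested in a Data Safety Monitoring Board". Protocol 10.1 describes what the board does: "The DSMB will review all serious adverse events reports in real-time and will receive periodic reports of all non-serious adverse events". The same section has the DSMB determine whether the study continues, is modified or stops on safety grounds. Sections 9.1.1.1 and 9.1.2.1.1 say that it may pause vaccination after an ad hoc review.

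Protocol 9.5 sets the reporting times:

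- SAEs that the investigator suspects are related to the vaccine are to be "telephoned to the local medical monitor and to Triclinium immediately upon" the investigator learning of them.
- Every SAE is faxed within 24 hours, which 9.5 equates with one calendar day, "of the investigative site becoming aware of the event to the local medical monitor and to Triclinium".
- The board's own limit is a separate sentence covering all SAEs: "Triclinium will notify the DSMB of all SAEs within three working days of becoming aware of an event".

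Other provisions bear on urgency. Under 9.1.2.1 the local medical monitor "will be immediately available to discuss the significance and possible impact of a SUSAR/SAE with the principal investigator". Under 9.1.2.1.1, where there is a safety concern, "the Local Medical Monitor in collaboration with the Principal Investigator will request that the Sponsor convene an ad hoc review" by the DSMB; 9.1.1.1 gives the investigator authority to ask for the same. Under 9.1.1 the investigator may delay an individual subject's dose on suspicion of significant risk.

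**The concern.** Two current sections describe the same flow of information at different speeds. Section 10.1 has the board reviewing SAE reports in real-time. Section 9.5 lets the report take three working days to arrive after the CRO already has it. The fast notices in 9.5 go to the monitor and the CRO, and the DSMB is on neither.

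What is at stake is subject safety. Neither the estimate nor the test of the primary endpoint is affected. If a related death or a life-threatening reaction occurs, the body that can pause vaccination across the study has no guarantee of hearing promptly, and dosing of other subjects may continue meanwhile.

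**Working it through.** **Inputs.** The limit is three working days from CRO awareness (9.5). The fax limit is one calendar day from site awareness (9.5). The telephone notice is immediate (9.5), so site and CRO awareness fall on the same day for a related SAE. Assumptions: working days are Monday to Friday, the count starts the day after awareness, and there are no public holidays.

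**Step 1: three working days in calendar days, from CRO awareness.**

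| CRO aware | Limit falls on | Calendar days |
|---|---|---|
| Mon | Thu | 3 |
| Tue | Fri | 3 |
| Wed | Mon | 5 |
| Thu | Tue | 5 |
| Fri | Wed | 5 |
| Sat | Wed | 4 |
| Sun | Wed | 3 |

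The range is 3 to 5. The sum is 28, so the mean is 28/7 = 4.0 if awareness is spread evenly over the week. This is the permitted lag for a related SAE that has been telephoned.

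**Step 2: the same limit from site awareness, by the 24-hour fax.** Lag = 1 day + the step 1 value for the following weekday.

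| Site aware | Calculation | Calendar days |
|---|---|---|
| Mon | 1 + 3 | 4 |
| Tue | 1 + 5 | 6 |
| Wed | 1 + 5 | 6 |
| Thu | 1 + 5 | 6 |
| Fri | 1 + 4 | 5 |
| Sat | 1 + 3 | 4 |
| Sun | 1 + 3 | 4 |

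The range is 4 to 6. The sum is 35 and the mean 35/7 = 5.0.

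**Step 3: holidays.** These lengthen the limit. If the CRO learns of the event on a Thursday and the following Friday and Monday are both holidays, the three working days are Tuesday, Wednesday and the next Thursday, which makes 7 calendar days.

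**Step 4: effect of the fix.** A related SAE passed on with the telephone notice has a limit of 0 days, so the reduction is 3 to 5 minus 0 = 3 to 5 days. A fatal or life-threatening SAE passed on when the fax is received has a limit of 1 day from site awareness, so the reduction is 4 to 6 minus 1 = 3 to 5 days.

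**What cannot be computed.** The protocol gives no dosing rate, so the number of doses given during the lag is not derived here.

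**The case against.** The best counter-argument is that there is no contradiction. Section 10.1 sets real-time review of SAE reports against periodic reports of non-serious events, so the phrase may mean case by case on arrival instead of in batches. On that reading 9.5 governs when the report arrives and 10.1 how it is then handled. The change summary in 17.2 lends some support: the revision that rewrote 10.1 also edited the 9.5 sentence and kept the three working days. This softens the conflict but does not remove it. Review of a case that may arrive 3 to 5 calendar days after the CRO has it is hard to call real-time, and this reading provides no faster notice for the gravest events.

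Second, an urgent path exists. Related SAEs are telephoned at once, the monitor is available immediately and is the sponsor's representative, and a safety concern leads to a request for ad hoc DSMB review. That may well reach the board before the limit. It still depends on someone judging that a concern exists, and it does not make the DSMB a recipient of the notice.

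Third, this is a single-site trial. The investigator can hold doses subject by subject, doses 2 and 3 have a window of plus 7 days, and Day 0 can be rescheduled. A hold of 4 to 6 days will often fit without losing a dose. This reduces exposure, but it is discretionary and is not a study-wide pause.

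A reader might go further and infer that the DSMB is the last to hear of an SAE. The documents do not show this: 9.5 does not state the reporting times to the regulator and the ethics committee, so no ranking is possible. A reader might also count the absence of a deadline for the ad hoc review as a separate fault. That is not claimed here: the ad hoc route supplements routine notification, and the remedy is prompt notice in 9.5.

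**Conclusion.** The point holds as a cheap improvement for patient safety. Sections 9.5 and 10.1 do not fit together, and no text guarantees the DSMB prompt notice of a related, fatal or life-threatening SAE. The permitted lag is 3 to 5 calendar days from CRO awareness, or 4 to 6 from site awareness through the 24-hour fax. Both ranges assume a Monday to Friday week without holidays.

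These figures are ceilings. It would be wrong to read them as the delay to expect, because earlier notice is allowed and the safeguards above may act first. Nothing here bears on randomisation, blinding or the primary analysis, and faster notice does not by itself ensure a faster decision.

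**What to change.** In Protocol 9.5, replace the three-working-day limit with a requirement that the CRO forwards SAEs to the DSMB as follows:

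- Related SAEs: at the time of the immediate telephone notice.
- Fatal or life-threatening SAEs: on receipt of the 24-hour fax.
- All other SAEs: on receipt, so that 9.5 matches 10.1.

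Decisions to pause or stop stay with the DSMB.

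The cost is one reworded sentence and the forwarding of notices that already exist. First reports to the DSMB will be less complete. Section 9.5 already accepts this for the monitor and the CRO, since investigators are told not to wait "to collect additional information to fully document the event before notifying the local medical monitor and Triclinium of a serious adverse event", and it already requires timely follow-up information to the DSMB.

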## 9.6 Other Events Requiring Immediate Reporting

The investigator must report the following events by faxing the appropriate form to the local medical monitor and Triclinium within 24 hours of becoming aware of the event; Triclinium will forward the appropriate form to ISS:

- Withdrawal of consent during the study (Immediately Reportable Event Form)
- Emergency un-blinding (Immediately Reportable Event Form)

- Protocol violation affecting the safety of a subject or involving the vaccination process (Immediately Reportable Event Form)
- Adverse event thought to be an allergic reaction to the study vaccine (Immediately Reportable Event Form, unless event meets SAE criteria)
- Any event that, in the opinion of the investigator, precludes further administration of the study vaccine (Immediately Reportable Event Form, unless meets SAE criteria)
- Pregnancy (Immediately Reportable Event Form, and Pregnancy Notification Form)

In each case the investigator will make every effort to keep the subject in the study until the end of the follow-up period (week 48); if this is not possible, the final follow-up investigations will be conducted at the time of study termination. In case of study termination, the subject will be managed in accordance with the investigator's clinical judgment.

In case a subject misses a scheduled vaccination visit, the study staff will try to establish communication with him/her through all possible means (e.g., call the subject, contact his/her ARV clinic,) and will attempt to reschedule the vaccination visit within the 7 day window period; after this period the subject will be withdrawn from further vaccination, on the basis of a non-compliance to the protocol.

The requirement to attend all scheduled study visits will be emphasized to subjects at each visit.

### **9.7 Follow-up of Subjects Who Become Pregnant**

Female subjects will be advised of the unknown risk of study vaccine to the unborn fetus and will be advised to use adequate birth control methods for at least 3 weeks prior to vaccination and for the whole the duration of the study.

If a subject becomes pregnant during the study, she should be encouraged to continue in the study for safety follow-up. Follow-up should continue for pregnancy outcome including premature terminations, and data are to be included in the safety reports.

The investigator must notify the Local Medical Monitor and Triclinium of the pregnancy immediately (even if already known to have resulted in spontaneous or elective abortion) by fax. At a minimum, the estimated date of conception, the estimated due date, and the date the subject received the study vaccine should be provided.

If a subject becomes pregnant, she will not have blood drawn as normally mandated by the protocol, but will undergo all other evaluations according to the Schedule of Procedures.

The health status of the mother and child, the date of delivery, and the child's sex and birth weight should be reported after delivery. If delivery occurs before the final study visit, the subject should continue to be followed for SAEs through the final study visit unless withdrawal of consent has occurred. If delivery occurs after the final study visit, the investigator should attempt to maintain contact with the subject to obtain information after delivery.

Pregnancy will not be recorded as an adverse event. If the pregnancy results in a miscarriage or a planned termination, the event (spontaneous abortion or elective abortion) will be reported as an adverse event or a serious adverse event per the investigator's judgment (e.g.,

if it was a medically important or life-threatening event that meets the definition of a serious adverse event).

A congenital anomaly or birth defect (i.e., an adverse finding in a child or fetus of a subject) within 12 months of the last exposure to the IP, must be reported as a serious adverse event.

If it is determined after completion of the study that a subject became pregnant during the study, the subject should notify the investigator. The pregnancy must be reported to Triclinium, and the status of the mother and child after delivery will be obtained and reported, when possible.

Male subjects will be advised of the unknown risk of study vaccine to the unborn fetus and will be advised to use adequate birth control methods (condoms) for the whole the duration of the study.

### **9.8 Subject Diary and Temperature Monitoring**

Subjects will receive, and be instructed in, the operation of a daily adverse event diary and a thermometer to be used during the 7-day post-vaccination diary period after vaccine administration. The daily adverse event diary is a source document and will record solicited adverse events, daily thermometer assessments of body temperature, and any other adverse events. At the safety visits scheduled 7 days after each vaccination the diary card will be collected and reviewed by the principal investigator (or designee) at which time any clinical details required for complete understanding of the information recorded will be obtained. Diaries not brought to the scheduled visit should be obtained before adverse event assessment can be performed. Lost diaries will be reconstructed as possible on a new diary booklet by the subject from memory at the closest clinic visit and labeled as a reconstructed diary. Adverse events obtained from the diary will be recorded and completely assessed on the Adverse Event CRF. Body temperatures below 38° C will not be considered fevers.

Any change to an AE recorded by the subject on the diary card (e.g., the severity level of an event is changed after interviewing the subject) based on the investigator's evaluation of the event must be explained by notation in source documentation.

## **10 STUDY PAUSE/STOPPING RULES**

### **10.1 General rules for a study pause**

The Sponsor will appoint an independent DSMB to monitor the safety of the subjects enrolled in the study. The DSMB will review all serious adverse events reports in real-time and will receive periodic reports of all non-serious adverse events; the DSMB may un-blind any amount of safety information needed to conduct their assessments. The DSMB will determine whether the study should be continued, modified or stopped for safety concerns. Guidelines for making such a decision will be developed by the Sponsor in consultation with the DSMB.

### **10.2 Premature Discontinuation of the Study**

ISS may stop the conduct of the trial at the clinical site for any of the following reasons:

- the site cannot include an adequate number of subjects
- significant and/or persistent non-compliance with the protocol
- careless or premeditated false documentation in the CRFs

- inadequate co-operation with the Sponsor
- non-compliance with ICH GCP, SOPs or the applicable regulatory requirements
- the investigator requests to discontinue the trial
- lack of confidentiality and/or non-compliance with the contractual agreement with the Sponsor.

If the trial is prematurely terminated or suspended, ISS will inform the investigators/institutions, and the regulatory authority and IEC/s, providing the justification for this course of action. All the subjects involved in the study will be informed promptly and appropriate follow-up and if relevant treatment will be assured.

## **11 DATA RECORDING, MONITORING AND DATA MANAGEMENT**

### **11.1 Data Recording**

#### **Case Report Forms**

All subject data generated by the study will be recorded on the CRFs provided. All original entries should be initialed and dated by the individual conducting the assessment. The forms will consist of 3-part no-carbon-required paper and should be completed in black ink (hard point pen).

Any correction or deletion should be made by drawing a single line through the entry so that the original entry is still legible. This change must be initialed and dated by the site study coordinator or Investigator. The top 2 pages will be collected by the study monitor. The bottom page should be retained by the Principal Investigator, and must be made available for review by the Sponsor, Institutional Review Board (IRB), or appropriate regulatory agencies.

Any changes made to data after collection of the CRF pages by Data Management will be made through the use of Data Clarification Forms (DCF). Data reported on the CRFs, which are derived from source documents, should be consistent with the source documents or the discrepancies should be explained. Case Report Forms will be considered complete when all missing and/or incorrect data have been resolved.

#### **Source Documentation**

Source documents are considered to be all information in original records and certified copies of original records of clinical findings, observations, data or other activities in a clinical study necessary for the reconstruction and evaluation of the study.

Source documents will be maintained for all data collected in the CRFs.

Investigators are required to prepare and maintain adequate and accurate case histories designed to record all observations and other data pertinent to the investigation on each individual entered into the study. Data reported on the Case Report Form (CRF) must be consistent with the source documents.

### **11.2 Data Monitoring**

This trial will be conducted in accordance with the principles of Good Clinical Practice. Before clinical trial initiation, Triclinium personnel will visit the clinical site to:

- determine the adequacy of the site facilities

- discuss with the investigator(s) (and other personnel involved in the study) their responsibilities with regard to protocol adherence, and the responsibilities of Sponsor or its representatives.

During the study, a Clinical Trial Monitor will have regular contacts with clinical site, including visits to:

- provide information and support to the investigator(s)
- confirm that facilities remain acceptable
- confirm that the investigational team is adhering to the protocol, that data are being accurately recorded in the case report forms, and that investigational product accountability checks are being done
- perform source data verification (a cross-check between data recorded in CRF and subjects' medical records and/or other records relevant to the study). This will require direct access to all original data for each subject (e.g. clinical records).

